### Plans to promote participant retention and complete follow-up {18b}

The potential benefits of inulin supplementation for preventing complications in patients with migraines will be discussed to encourage their full participation in the study. The research team will maintain regular contact with participants via telephone. Additionally, they will employ strategies to enhance participant retention, such as sending reminders for taking the supplementation and scheduling post-intervention visits.

### Data management {19}

One of the researchers will oversee the coding, security, and storage of data. Data will be entered electronically at the participating site, and the forms will be securely stored on file. Furthermore, they will double-check data entry and values. If any patient reports adverse events, additional information will be gathered to determine whether to exclude them from the study. According to the Medical Ethics Committee Criteria, unblinding is permissible in this situation, allowing us to specify whether the patient received inulin or a placebo.

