#### Criteria for discontinuing or modifying allocated interventions {11b}

Patients may withdraw from the trial at any time for any reason. The investigator may withdraw patients from the trial to protect their safety or if they are unable or unwilling to continue with the trial. Furthermore, the reasons for each patient’s withdrawal from the trial will be explained in detail in the study results.

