#### Concealment mechanism {16b}

To ensure blinding, packs of inulin or placebo will be labeled as A and B by an independent person who is not involved in the trial. Both patients and investigators will be unaware of the treatment assignment. The allocation sequence will be concealed from those assigning patients to the intervention groups using opaque sealed envelopes. Randomization codes will only be unlocked after all participants have completed the trial protocol.

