#### Procedure for emergency unblinding if needed {17b}

The labels on the supplements will only be revealed at the final analysis stage of the study. Any unblinding that occurs during the study will be recorded and reported in the Iranian Registry of Clinical Trials, the Ethics Committee of Isfahan University of Medical Sciences, and in the final results of the study.

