### Adverse event reporting and harms {22}

According to previous studies, supplementation with inulin at a dosage of 10 g per day has been found to be safe and devoid of serious side effects [39, 40]. In the event of any complications arising from inulin supplementation, the intervention will be promptly discontinued, and the necessary medical measures will be taken. Any potential adverse effects will be reported to the Ethical Committee of Isfahan University of Medical Sciences. Based on the severity and nature of the adverse effects associated with supplementation, the ethical committee will determine whether to exclude the patient from the study or assign an exclusive code or undertake other appropriate actions.

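### The study team may learn a patient's arm while her exclusion for an adverse event is being decided; no clinical-need condition is stated, and the two code-release rules name no matching exception

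*Protocol article*

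**What the plan says.** Four parts of the protocol article bear on when the code may be opened and on who decides that a patient stops.

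- **Data management {19}** describes the trigger: "If any patient reports adverse events, additional information will be gathered to determine whether to exclude them from the study". The next sentence gives the permission: "According to the Medical Ethics Committee Criteria, unblinding is permissible in this situation, allowing us to specify whether the patient received inulin or a placebo".
- **Concealment mechanism {16b}** sets the general rule: "Randomization codes will only be unlocked after all participants have completed the trial protocol". No exception is attached.
- **Procedure for emergency unblinding if needed {17b}** has a similar rule for pack labels: "The labels on the supplements will only be revealed at the final analysis stage of the study". It then foresees earlier breaks: "Any unblinding that occurs during the study will be recorded and reported in the Iranian Registry of Clinical Trials", as well as to the ethics committee and in the final results. It gives no criterion for when a break is permitted.
- **Adverse event reporting and harms {22}** places the exclusion decision with the ethics committee: "Based on the severity and nature of the adverse effects associated with supplementation, the ethical committee will determine whether to exclude the patient". Separately, Criteria for discontinuing or modifying allocated interventions {11b} says: "The investigator may withdraw patients from the trial to protect their safety or if they are unable or unwilling to continue".

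People who will be blind {17a} states that investigators and patients are both unaware of the assigned group.

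**The concern.** A code break in a blinded trial normally serves one purpose: to give those treating a patient information that they need to care for her. Here the permission is tied to a different moment, when her exclusion is under consideration. Nothing in that section says that the exclusion decision comes first, or that it is taken blind.

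Two things are at stake. First, if the arm is known when the decision is taken, stopping could come to differ between the arms for reasons other than the event itself. An identical gastrointestinal complaint might be judged differently once the patient is known to be on inulin or on maltodextrin. Second, headache frequency, the primary outcome in Outcomes {12}, is assessed by a neurologist and through patient questionnaires. It is open to influence if the assessor or the patient learns the arm and she is assessed afterwards.

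There is also a practical problem. Staff facing an adverse event find one section that permits unblinding and two that appear to rule it out before the end, with no cross-reference to show which governs.

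**Working it through.** No arithmetic applies: the plan states no figure on this point, and the question is what the sections say when read together.

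**Step 1. What situation triggers the permission?** The permission in Data management {19} refers back to the sentence before it. That sentence contains two elements: a patient has reported an adverse event, and information is being collected to settle whether she is excluded. Whichever element is stressed, the permission covers the time when exclusion is undecided.

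**Step 2. Is there a limiting condition?** The section states neither a severity threshold nor a requirement that treatment depends on the arm. It refers to ethics committee criteria, which may contain such a limit, but the article does not reproduce them. Unblinding is permitted, not required.

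**Step 3. Who learns the arm?** The permission is worded in the first person plural, so the recipient is the study team, not an independent treating clinician. Section {17a} describes the investigators as blind. Composition of the coordinating center {5d} gives recruitment, treatment and follow-up to the principal investigator and research physician. No section separates those who receive the code from those who assess outcomes.

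**Step 4. Do the code-release rules allow for it?**

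| Section | Rule | Exception stated |
|---|---|---|
| {16b} | Codes opened only when every participant has finished | None |
| {17b}, first sentence | Labels revealed only at final analysis | None |
| {17b}, second sentence | Earlier breaks are recorded and reported | Foresees breaks; no criterion |
| {19} | Break permitted when an adverse event is reported and exclusion is being considered | Not cross-referenced to {16b} or {17b} |

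A break under {19} before the last participant finishes departs from {16b} as written. The second sentence of {17b} softens the conflict, because it shows that the authors expected some breaks, but it does not settle when one is proper.

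**Step 5. Who decides on stopping, and on what basis?** Section {22} gives exclusion to the ethics committee, on how serious the event is and of what kind. Section {11b} also lets the investigator withdraw a patient for safety. Neither makes the arm a criterion, and neither says that the decision is taken without it.

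**Step 6. What happens to the data of a stopped patient?** Interim analyses {21b} and section {20c} keep drop-outs and excluded patients in an intention-to-treat analysis with multiple imputation. An exclusion decided with the arm known therefore need not remove her from the analysis set. It could still end her treatment. Table 1 schedules clinical features only at week 1 and at close-out, and no section says that a stopped patient returns for the final assessment. Her endpoint may then be imputed rather than observed.

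**The case against.** The strongest reply has four parts.

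1. **The permission is not open-ended.** It is given under ethics committee criteria, and a condensed article commonly leaves the detailed code-break procedure to the full protocol. This stands in part: nobody can say from the article that no limit exists. The point is confined to what the article states, which is a permission attached to the exclusion decision.

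2. **The sections are a default and its exception.** Section {17b} is headed as an emergency procedure and expects breaks to be reported. This is a fair reading and reduces the conflict to one of wording. But the two rules say "only" in substance and point to no exception, so the reader must supply the link.

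3. **The trigger may be narrow.** Section {21b} describes adverse events by examples such as death, disability and severe allergic reaction. If {19} means only those, breaks would be rare and mostly justified. Against this, Table 1 schedules adverse events in each of the 12 supplementation weeks, which suggests a wider use of the term. The article does not settle the matter.

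4. **The route to bias is thin.** A patient who is excluded and not assessed again cannot have a biased later assessment. This is correct for assessor bias. It does not answer the concern about how the stopping decision itself was reached.

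Three stronger readings are tempting, and the document does not support them. A reader might infer that the arm is meant to decide exclusion; no section says so, and {22} points to the nature of the event. A reader might infer from the labelling in {16b} ("packs of inulin or placebo will be labeled as A and B by an independent person who is not involved in the trial") that one break reveals every other patient's arm; that would hold only if packs carry no individual number and the person who learns the code sees the other labels, and the article states neither. A reader might also treat the whole period during which codes are meant to stay closed as a measure of the damage; it is only the length of the trial and says nothing about bias.

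**Conclusion.** The point holds in a limited form. The article permits the study team to learn a patient's arm while her exclusion for an adverse event is being decided, states no condition that her care needs it, and names no such exception in the two sections that restrict code release. As written, stopping could be decided with the arm known by people whom the article describes as blind.

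The size of any effect cannot be computed. It depends on how many breaks occur, how broadly an adverse event is understood, and what the ethics committee criteria say; none of these is given. Retention of excluded patients under intention-to-treat limits the effect on the analysis set, provided that this rule is followed. This is a change that should be made because it is cheap and removes an avoidable route to bias. It does not show that the trial's result is or will be biased. Confidence is medium, mainly because the committee criteria are not shown.

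**What to change.** In **Data management {19}**, state that:

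- the decision to stop or exclude a patient is made and recorded without knowledge of her arm;
- the code is broken only when her clinical care needs it, and in an emergency immediately, without waiting for that record;
- the result goes only to those treating her and not to outcome assessors.

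In **Concealment mechanism {16b}** and **Procedure for emergency unblinding {17b}**, name this as the sole exception to the rules on opening codes and labels. The reporting requirement in {17b} can stay as it is.

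If the ethics committee criteria already contain such a limit, quoting it in {19} would meet the second item. The change takes no view on which clinical events should lead to stopping.

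The cost is a wording amendment through the ethics committee and a short written record before any non-emergency break. No additional assessor is needed.

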### Confidentiality {27}

Each participant will be assigned a unique study identification code, which will be used to store research data. The research team will have access to the code list during the study, which will be documented and protected by the principal investigator according to research guidelines after the study concludes. Personal details of participants will not be disclosed in any publications.

### Plans for collection, laboratory evaluation, and storage of biological specimens for genetic or molecular analysis in this trial/future use {33}

Laboratory assessments will be conducted at the beginning and conclusion of the study. A 10-ml blood sample will be obtained after a 12-h fasting period and centrifuged for 10 min at a speed of 2500 rpm at room temperature. The serum samples will be divided into microtubes and promptly frozen at − 70 °C. The levels of zonulin and Hs-CRP in the serum will be measured using ELISA (ZellBio, Germany) and turbidimetric (BIOREX, Iran) assay kits, respectively. The serum levels of TOS, TAC, and NO status will be assessed using the Fox1, Cuprdc, and Griess methods, respectively, with the aid of commercial kits (Kiazist Life Sciences, Iran). The Oxidative Stress Index (OSI) will be calculated using the following formula: OSI = [(TOS, μmol/l)/ (TAC, μmol/l) × 100].

### Statistical methods

#### Statistical methods for primary and secondary outcomes {20a}

Statistical analyses will be conducted using SPSS (version 21.0) software. A *P*-value < 0.05 will be considered statistically significant. The one-sample Kolmogorov–Smirnov test will be used to evaluate the normality of the distribution of data. Regarding missing values, the data analysis will be subjected to intention-to-treat (ITT) analysis. We will employ the multiple imputation approach to perform ITT. In order to compare the baseline value of qualitative and quantitative variables, the chi-square test and *t*-test will be used. Categorical variables will be expressed as number and percentage, while quantitative data will be presented as mean ± standard deviation. Between-group differences will be evaluated using a Mann–Whitney *U* test and independent *t*-test. Differences within the group will also be assessed with a Wilcoxon rank-sum test and paired *t*-test. To control for confounders, an analysis of covariance (ANCOVA) will be carried out.

The primary results of this study include the evaluation of clinical symptoms of patients, such as headache frequency, duration, and severity. The secondary results encompass the evaluation of the serum levels of zonulin, Hs-CRP, TAC, TOS, NO, mental health status, and QOL by questionnaire.

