### Sample size {14}

The sample size for the present study was calculated based on means and standard deviations for the frequency of attacks, as the main outcome of the study of Ghavami et al. [41], by considering a 95% confidence interval and 80% power (*α* = 0.05 and *β* = 0.2). Frequency of attacks was also considered a main outcome, and based on a previous study, the sample size was calculated as 40 patients for each group. All patients who meet the inclusion criteria and are willing to participate in the trial will be included until the estimated sample size is completed.

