### Assignment of interventions: allocation

#### Sequence generation {16a}

The present study will be conducted as a randomized double-blind, placebo-controlled study using a stratified randomization method. Stratified permuted block randomization will be employed to balance age (20–35 and 35–50 years) between the two groups over time. Within each of the aforementioned strata, eligible patients will be randomly assigned in a 1:1 ratio to receive either inulin or placebo with a block size of four. A block size of four will be constructed in six different arrangements (blocks) which will be created for each stratum to assign patients to the trial groups. The sequence of these blocks will be generated for each stratum using a random number generator available at randomizer.org. A person not involved in the study will randomly divide patients into two groups: intervention (inulin, *n* = 40) and control (placebo, *n* = 40).

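### Baseline differences between randomised arms are to be significance-tested, and the ANCOVA is aimed at unnamed confounders instead of at the outcome's baseline value and the age stratum

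*Protocol article*

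**What the plan says.** All the relevant text on analysis is in the protocol article, section {20a} (statistical methods for primary and secondary outcomes).

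- Baseline comparison: "In order to compare the baseline value of qualitative and quantitative variables, the chi-square test and" the t-test will be used.
- Threshold: a P-"value < 0.05 will be considered statistically significant". No exception is made for baseline comparisons.
- Outcome comparison: "Between-group differences will be evaluated using a Mann–Whitney" U test and an independent t-test. Both are unadjusted.
- Adjustment: "To control for confounders, an analysis of covariance (ANCOVA) will be carried out". The section names no covariate, gives no rule for recognising a confounder, and does not rank the adjusted against the unadjusted result.

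Two other sections bear on this. Under sequence generation {16a}, "eligible patients will be randomly assigned in a 1:1 ratio to receive either inulin or placebo with a block size of four", within two age strata. Under outcomes {12}, the clinical symptoms, biomarkers, mental health and quality of life are measured at baseline as well as at the end. The two natural covariates, the outcome's own baseline value and the age stratum, are therefore known in advance and already collected.

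**The concern.** With concealed 1:1 randomisation, the hypothesis that the arms come from the same population at baseline is true by design. A small P is then a false alarm. A large P does not show that an imbalance in a strong predictor is harmless. For age the test is emptier still, because the allocation is stratified on it.

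Confounding is the language of observational studies. In a randomised trial a covariate earns its place because it predicts the outcome, whether or not the arms happen to differ on it. Framing ANCOVA as control of confounders, beside a set of baseline significance tests, leaves two things open:

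1. Covariates may be picked because of a chance P < 0.05. A covariate picked by that rule enters in about 5% of trials, however strongly it predicts attacks.
2. With unadjusted tests and an ANCOVA both planned and neither given precedence, the preferred result may be chosen after the data are seen.

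At stake are power that the trial could have at no extra cost and protection of the primary comparison from a challenge about post-hoc adjustment.

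**Working it through.** **Plan's own figure.** The sample size section {14} says that "the sample size was calculated as 40 patients for each group", "by considering a 95% confidence interval and 80% power". It takes means and standard deviations from an earlier study but prints neither, so 40 per arm cannot be reproduced. It can be inverted. Two-sided 5% is assumed, since sidedness is not stated.

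- Normal approximation: d = (1.960 + 0.842) × √(2/40) = 2.802 × 0.2236 = 0.626 SD.
- With the t distribution: d = 0.634 SD. This value is used below.

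**Chance baseline findings.** For k independent tests at 0.05, the expected number significant is 0.05k and the chance of at least one is 1 − 0.95^k. The article's baseline variables come to about 25 if grouped (gastrointestinal problems, medication and diet once each) and about 33 if indices and markers are all counted. Both counts are my own.

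| k | Expected | At least one |
|---|---|---|
| 10 | 0.50 | 40% |
| 25 | 1.25 | 72% |
| 33 | 1.65 | 82% |

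The last two chances are too high as they stand, because many variables overlap. The three migraine indices are products of frequency, severity and duration, the oxidative stress index is a ratio of two other markers, and the body measures are related. With 33 variables and an illustrative common correlation of 0.2 or 0.4, the chance falls to 75% or 61%.

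**Gain from always adjusting.** Adjusting for a baseline value with correlation ρ to the end value shrinks the residual SD by √(1 − ρ²), so the effective difference is 0.634/√(1 − ρ²). Approximate power is Φ(effective d × √20 − 1.96).

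- ρ = 0.3: 0.634/0.954 = 0.665; Φ(1.01) = 84%.
- ρ = 0.5: 0.634/0.866 = 0.732; Φ(1.31) = 91%.
- ρ = 0.6: 0.634/0.800 = 0.793; Φ(1.58) = 94%.
- ρ = 0.7: 0.634/0.714 = 0.888; Φ(2.01) = 98%.

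**Simulation.** 20,000 trials per case, 40 per arm, one normal baseline covariate, d = 0.634 for power and d = 0 for type I error. Test-then-adjust means ANCOVA only when the baseline test gives P < 0.05, and the unadjusted test otherwise.

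| ρ (assumed) | Power, always adjusted | Power, test-then-adjust | Type I, test-then-adjust | Type I, better of the two results |
|---|---|---|---|---|
| 0.3 | 83% | 80% | 5.0% | 6.7% |
| 0.5 | 90% | 81% | 4.2% | 7.1% |
| 0.6 | 94% | 82% | 3.8% | 7.5% |
| 0.7 | 97% | 82% | 3.7% | 8.3% |

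Unadjusted power is 80% throughout. The simulated power for always adjusting agrees with the formula to within about a point. A separate run at ρ = 0.3, 0.5 and 0.7 gave type I errors of 4.8%, 4.3% and 3.7% for test-then-adjust, and 6.4%, 7.5% and 8.2% for the better of two. Differences of a few tenths of a point are simulation noise.

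**The case against.** The strongest objection is that the link between the two sentences is inferred. A reader might conclude that covariates will enter the ANCOVA because of a significant baseline test. The article does not say so. The sentences stand apart, with data presentation and the outcome tests between them, and confounders could equally mean known prognostic factors fixed elsewhere. This stands: selection by baseline test is permitted, not planned, and the test-then-adjust figures apply only if that rule is followed.

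A second objection is that this is a condensed article and no analysis plan is shown, so a missing covariate list is not a fault in itself. That also stands. The point rests on what section {20a} does state: significance tests of baseline, unadjusted outcome tests, and adjustment aimed at confounders. A covariate list held elsewhere would not remove the stated baseline tests.

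Third, P values in a baseline table change no treatment estimate. This is true of the tests alone. It does not cover the unadjusted comparison or the open choice between two results.

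Fourth, a reader might infer that choosing covariates by baseline test inflates false positives. It does not: that rule is slightly conservative. Inflation arises only if the more favourable of the adjusted and unadjusted results may be reported.

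Finally, the power gain depends on an unknown correlation and is only about 3 points at 0.3.

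**Conclusion.** The point holds in a limited form. Section {20a} plans significance tests that have no useful null hypothesis in a randomised trial. It also describes adjustment in a way that ties it neither to the outcome's baseline value nor to the stratification factor. It leaves open both how covariates are chosen and which result governs.

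The main cost is forgone power. Always adjusting gives about 83% to 97% over assumed correlations of 0.3 to 0.7, against about 80–82% if the analysis is unadjusted or adjusted only after a significant baseline test. Type I error would be about 5.0% falling to 3.7% under test-then-adjust, and about 6.7% to 8.3% under free choice of the better result. At least one chance baseline difference is to be expected in about 72–82% of trials if 25 to 33 variables are independent, and less often because many are correlated.

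These figures assume two-sided 5% tests, normal data, a single covariate and a true difference of 0.634 SD; the article supplies no effect size or correlation. The change should be made, but nothing here invalidates the trial.

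**What to change.** In section {20a}:

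1. Delete the chi-square and t-tests of baseline variables, and present baseline data by arm descriptively, without P values.
2. Make the between-group analysis an ANCOVA with the outcome's own baseline value and the age stratum as covariates, fixed before unblinding. State that this result governs and that any unadjusted comparison is supportive.
3. State that no covariate is added or dropped because of an observed baseline difference.

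The cost is one sentence deleted and one or two added. All the data are already collected, and recruitment, treatment and sample size are unaffected.

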**Methods:**

This is a randomized, double-blind, placebo-controlled clinical trial involving 80 women with migraine who meet the inclusion criteria (aged between 20 and 50 years with a diagnosis of migraine by a neurologist based on the ICDH-3). Participants will be assigned to receive a daily dose of 10 g of inulin for 12 weeks (intervention group, *n* = 40) or 10 g of maltodextrin as a placebo for the same duration (control group, *n* = 40). The primary outcome will measure the variations in the frequency of headache experienced by the patients. Secondary outcomes will encompass serum levels of zonulin, high-sensitive C-reactive protein, total antioxidant capacity, total oxidant status, nitric oxide, mental status, QOL, duration, and severity of migraine attacks.

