**Fig. 1 Fig1:**
[figure not shown]
The protocol flow chart and timeline of the study

**Table 1 Tab1:** Schedule of enrollment, intervention, and assessment based on SPIRIT guidelines

		Registration	Allocation	Post-Allocation												Close-out
Time point (week)		-W_1_	W_0_	W_1_	W_2_	W_3_	W_4_	W_5_	W_6_	W_7_	W_8_	W_9_	W_10_	W_11_	W_12_	W_13 (starting)_
Registration	Eligibility testing	*														
	Informed consent	*														
	Randomization		*													
	Allocation		*													
	Patient instruction			*												
Intervention	Supplementation			*	*	*	*	*	*	*	*	*	*	*	*	
	Compliance			*	*	*	*	*	*	*	*	*	*	*	*	
	Adverse events			*	*	*	*	*	*	*	*	*	*	*	*	
Assessment	Demographic			*												*
	Anthropometric indices			*												*
	Physical activity			*												*
	Dietary intake			*												*
	Mental status			*												*
	Quality of life			*												*
	Clinical features			*												*
	Biochemical assays			*												*
	Supplement checklist															*

Demographic variable including: type of migraine (episodic and chronic), age, anthropometric indices, education status (university graduated, and non-university graduated), marital status (single and married), migraine in first relatives, gastrointestinal problems (bloating, constipation and diarrhea), medication (beta-blockers, anticonvulsant drugs, Tricyclic Antidepressants (TCA), Tetracyclic Antidepressant (TeCA), Serotonin-Norepinephrine Reuptake Inhibitor (SNRI) or mixture of them); Anthropometric indices including: body weight (BW), body mass index (BMI) and waist circumference (WC); Mental including: depression, anxiety, stress; Quality of life including: migraine Specific Quality of Life (MSQ) and the headache impact test-6 (HIT-6); Clinical features including: frequency, severity, duration; Biochemical assays including: serum zonulin, High-sensitive C reactive protein (Hs-CRP), total antioxidant capacity (TAC), total oxidant status (TOS), nitric oxide (NO)

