##### Migraine symptoms assessment

Clinical features of migraine at the initiation and end of the intervention were obtained from all participants. The migraine symptoms, such as headache frequency (number of attacks per month), severity, and duration (mean duration of headache attacks in a day per month) will be assessed by a neurologist. Participants will then be asked to complete questionnaires regarding the duration and frequency of the attacks during the intervention. The severity of pain will be assessed using a VAS ranging from 0 to 10. Participants will be instructed to score 0 if they experience no pain and 10 if they suffer from agonizing pain. The headache impact test-6 (HIT-6) scale will also be used to evaluate the degree of disability due to migraine at baseline and at the end of the trial. The HIT-6 questionnaire examines the patient’s disability as a score. The reliability and validity of this questionnaire have been established in an Iranian population [43]. Moreover, clinical symptoms of migraine, such as the migraine headache index score (MHIS), headache diary result (HDR), and migraine index (MI), will be calculated using the following formula:$$\mathrm{MI }=\mathrm{ frequency }\times \mathrm{ severity}$$$$\mathrm{HDR }=\mathrm{ frequency }\times \mathrm{ duration}$$$$\mathrm{MHIS }=\mathrm{ frequency }\times \mathrm{ duration }\times \mathrm{ severity}$$

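### The primary analysis is not fixed among a t-test, a Mann–Whitney test and an ANCOVA, and the ANCOVA names neither baseline attack frequency nor the age stratum

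*Protocol article*

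**What the plan says.** Section {20a} of the protocol article sets out the analysis in this order:

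- A one-sample Kolmogorov–Smirnov "test will be used to evaluate the normality of the distribution of data".
- Missing values are handled by multiple imputation under intention to treat, and baseline characteristics are compared by chi-square and t-test.
- "Between-group differences will be evaluated using a Mann–Whitney" U test and an independent t-test.
- After the within-group tests: "To control for confounders, an analysis of covariance (ANCOVA) will be carried out". No covariate is named.

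The article does not say which of these decides the primary outcome, or whether 12-week values or changes are compared. The abstract says: "The primary outcome will measure the variations in the frequency of headache experienced by the patients". That can be read either way.

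The baseline value of the outcome is available. Section {18a} says: "Clinical features of migraine at the initiation and end of the intervention were obtained from all participants", and it defines frequency as monthly attacks. Outcomes {12} and Table 1 also list a baseline and an end measurement. Section {16a} stratifies randomisation by two age bands, but {20a} does not mention age.

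**The concern.** A confirmatory trial needs one analysis that decides its primary outcome. Three are listed here, unranked, and they can disagree on the same data, so the choice could be made after the results are seen.

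The second issue is precision. Episodic and chronic migraine are both enrolled, so monthly attack frequency should vary widely between women, and each woman's own baseline should predict her 12-week value well. A t-test or Mann–Whitney test on 12-week values ignores that information. The ANCOVA could use it, but its stated purpose is confounding. Randomisation already deals with confounding in expectation. The reason to adjust in a randomised trial is prognostic strength and respect for the stratification, and that points to baseline frequency and age band, neither of which is named.

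A Mann–Whitney P-value also supplies no estimate with a standard error, so it does not fit directly with the planned pooling over imputations.

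**Working it through.** **Inputs from the article.** 40 per group, 1:1 allocation, "95% confidence interval and 80% power" (Sample size {14}; sections {14} and {16a}). Two-sided testing is assumed.

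**Inputs not in the article.** The means and SDs behind the sample size are not given, so the figure of 40 cannot be reproduced. The baseline/follow-up correlation ρ is not given either; 0.3 to 0.7 is assumed, with equal SDs at both visits.

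**Step 1: the effect implied by 40 per group.** With the two-sample normal formula, d = √(2/40) × (1.960 + 0.842) = 0.626. With the t distribution it is 0.634.

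**Step 2: power under each analysis.** If the 80% refers to an unadjusted comparison of 12-week values, the SD is multiplied by √(1 − ρ²) for ANCOVA and by √(2(1 − ρ)) for a change score. Power is Φ(2.802/factor − 1.960).

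| Assumed ρ | ANCOVA factor | ANCOVA power | Change-score factor | Change-score power |
|---|---|---|---|---|
| 0.3 | 0.954 | 83.6% | 1.183 | 65.8% |
| 0.5 | 0.866 | 89.9% | 1.000 | 80.0% |
| 0.7 | 0.714 | 97.5% | 0.775 | 95.1% |

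A change score does worse than ignoring baseline when ρ is below 0.5.

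**Step 3: does the gain survive if change scores were meant?** The variance ratio of ANCOVA to change score is (1 − ρ²)/(2(1 − ρ)) = (1 + ρ)/2, which is below 1 for every ρ below 1. If the 80% refers to change scores instead, ANCOVA power is Φ(2.802/√((1 + ρ)/2) − 1.960). That gives Φ(1.515) = 93.5% at ρ = 0.3, Φ(1.275) = 89.9% at 0.5 and Φ(1.079) = 86.0% at 0.7. ANCOVA is better on either reading.

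**Step 4: is validity at risk?** An illustrative simulation used 40 per group and 4,000 runs. Monthly counts were Poisson, with subject rates from a gamma distribution of mean 8 and extra gamma variation at follow-up. These distributions are invented for illustration.

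| Analysis | Type I error | Power at rate ratio 0.67 |
|---|---|---|
| t-test | 5.2% | 62% |
| Mann–Whitney | 5.4% | 59% |
| Chosen by Kolmogorov–Smirnov | 5.3% | 59% |
| Whichever of the two unadjusted tests is more favourable | 6.9% | 66% |
| ANCOVA on baseline | 5.0% | 75% |

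The Monte Carlo standard error at 5% is √(0.05 × 0.95/4000) = 0.34 percentage points. A pre-test applied as a fixed rule does almost no harm to type I error. An open choice between the two unadjusted tests inflates it modestly. The larger loss is power: 59% against 75% in this setting.

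**The case against.** The strongest objection is that the wording does not rule out a sound analysis. A reader might infer three things that the article does not say.

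- *That the Kolmogorov–Smirnov result picks the test.* This is the natural reading, but the text says only that normality will be assessed. How often such a check would reject cannot be inferred either. For an uncorrected test it was 4 to 11% in three assumed negative binomial settings at n = 40, and 53% in the null simulation above, where it was applied to all 80 values.
- *That an unadjusted test is the main one.* Nothing ranks the t-test or Mann–Whitney test above the ANCOVA.
- *That baseline frequency goes unused.* The abstract's wording may mean change from baseline, and the unnamed ANCOVA covariates may include it.

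All three corrections stand, and the point is limited accordingly. They do not remove it. If several readings are open, the primary analysis is not fixed, and step 3 shows that change scores do not recover the precision.

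A second objection is that a condensed article leaves detail to the analysis plan. That holds for the full covariate list, scales for skewed biomarkers and pooling rules, and none of these is held against the article. But {20a} is not silent on the comparison: it states three methods without an order and gives the adjustment a rationale that does not suit a randomised trial.

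Third, Table 1 marks the baseline measurements in W1, after allocation at W0 and in the first supplement column. A reader might infer that baseline is measured on treatment. Outcomes {12} places the first blood sample before the intervention and {18a} takes clinical features at its start, so this is mainly an ambiguity of the table.

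**Conclusion.** The point holds as one of pre-specification and precision. Section {20a} leaves the primary comparison open among three analyses. Two have no covariate, and the third does not name the two covariates that the design calls for. If 40 per arm gives 80% power for unadjusted 12-week values, baseline-adjusted ANCOVA raises it to about 84%, 90% or 97.5% at ρ of 0.3, 0.5 or 0.7, against 66%, 80% or 95% for change scores. These figures rest on assumed correlations, equal SDs at both visits, two-sided testing and a normal approximation.

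Two stronger conclusions are not supported. Nothing here shows that the treatment estimate would be biased: all the listed tests kept type I error close to 5% when fixed in advance. Nor does it show that 80 patients is the wrong number, because the article does not give the inputs needed to check it.

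**What to change.** In section {20a}, name one primary analysis: ANCOVA of 12-week monthly attack frequency on treatment group, baseline attack frequency and the age stratum used in randomisation. Report it as an adjusted difference with 95% CI, pooled over the planned imputations. State that neither a normality test nor baseline P-values will choose the test or the covariates. Keep the Mann–Whitney test as a sensitivity analysis, and replace the reference to confounders with the named covariates.

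As a side point, mark in Table 1 that the W1 baseline measurements are taken before the first supplement dose, consistent with Outcomes {12}.

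The cost is a few sentences and one table note. No further patients or measurements are needed. The change should be documented before the randomisation codes are opened.
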